**Figure 2 fig2:**
[figure not shown]
A study schematic including the time points when data collection occurs.

### Sample

2.2

The study sample will consist of adult FCGs. Inclusion criteria are as follows: (1) > 18 years of age; (2) caregiver of a patient who died from cancer during the past one year; (3) able to understand, speak, and read English; (4) able to hear conversation at a normal speaking volume; (5) have a phone and/or an email address where they can be reached; and (6) possess or have access to an internet-connected computer and/or a mobile device capable of displaying web pages. Exclusion criteria are (1) FCGs of persons who died of conditions other than cancer; and (2) FCGs of a patient who died from cancer more than 1 year ago.

### Procedures

2.3

Following IRB approval, convenience sampling will be used to recruit participants. Study eligibility will ultimately be determined by the project manager following evaluation of on-line eligibility responses. Recruitment will occur in a multi-pronged strategy: (1) study flyers will be posted at community sites including areas where support groups are held (hospice, campus); (2) letter distribution that will be mailed from a central state-wide hospice agency to FCGs who have lost their patient to cancer in past year that explains the study and provides information on how to contact the study project manager if interested in participating; (3) study posting on community social media websites such as Facebook; and (4) study registration on ResearchMatch, an on-line research volunteer registry. Strategies to recruit racially, ethnically, socioeconomically, and geographically diverse FCGs include ensuring broad representation of hospice sites that are in both urban and more remote rural areas that serve diverse populations (53). Further, filters will be applied that target racially and ethnically diverse populations when using the on-line research volunteer registry to increase a broader more representative group despite the convenience sampling methodology (53).

Interested potential participants complete informed consent prior to enrollment. All forms, surveys, and meditation modules are hosted on the secure HIPAA-compliant online platform, Qualtrics. To ensure eligibility, participants answer questions relative to the study eligibility criteria. Once confirmed, participants are assigned a unique three-digit study ID number for de-identification purposes and receive a link to complete the baseline Qualtrics surveys. Following completion of the Time 1 surveys, participants receive a link to the intervention modules, with orientation to the study. Study staff are available throughout the six-week period to conduct weekly check-ins, troubleshoot technical issues, and offer additional support to the FCG if needed.

At the end of the 6-week time, participants receive access to the Time 2 surveys, and again 6 weeks later at week 12 (Time 3). Participants receive a small gift card acknowledgement for their participation and continued access to the modules if desired. Fifteen participants will be interviewed using HIPAA compliant video-conferencing software to glean further information regarding the acceptability and feasibility parameters, and to identify any recommendations for wider-scale testing. Participants who consent to an interview will be contacted following completion of the week 12 surveys to schedule a date/time. The demographic and socioeconomic background of FCGs will be reviewed, and a representative sample will be invited to participate in the online interviews. With consent, these interviews will be recorded for data analysis purposes. The interview guide reflects questions that elicit important information relative to the NBHM experience, including both satisfaction and challenges in relation to acceptability and feasibility that can be used to strengthen the intervention on a larger scale.

### Intervention

2.4

Six modules integrating meditative practices with nature imagery were developed for online delivery, drawing on the strength of our team’s previous meditation and nature intervention work (54, 55), with input from a meditation therapist professional. Each module is framed and anchored to the same core constructs: attention restoration, grief awareness and processing, psychological wellbeing and promotion of QOL. Once the content was developed, each 15-to-20-min module was audio-recorded by the technical team with the verbiage delivered by an experienced meditation provider. A brief version (~10 min) of the same content was also recorded using a simulated voice for those with less time to commit to the practices or who might prefer an alternative voice. After the modules were recorded with both voice versions, all were alpha tested by research team members to identify overall functionality and to identify any problems needing addressment prior to use with actual bereaved CGs. All modules will be available to the enrolled CGs via a private online link through Qualtrics. The study project manager will send each participant the access link to all modules once baseline data is collected. The intervention modules include orientation to the content, clear guided instruction, and motivational content to support the establishment of a regular practice. The meditations are all designed to be done seated comfortably in a chair. Participants will be encouraged to wear headphones and eye masks to focus on the auditory experience.

### Fidelity

2.5

Standard NIH recommendations (dose, training, delivery, receipt, enactment) for socio-behavioral research will be used for intervention fidelity (56) and are depicted as following. Participants are asked to commit to completing a minimum of 4 modules over the 6-week period. The privately accessible website will record when an FCG accesses any module and the duration of use to establish doses received by individual participants. Because the intervention modules are pre-recorded and all training content on the web is uniform, there is no deviation in the provision of the intervention across participants. The intervention site which is accessible to study participants, records access and time spent with modules. Weekly emails, texts or calls (based on preference), using a toll-free access number during weeks 1–6, will provide reminders to engage with the nature meditations and to query if any technology assistance is needed. At week 12, meditation module access during the follow-up phase between weeks 7 to 12 will be monitored to assess sustained use of the intervention. All study staff will receive standardized training with active feedback prior to engaging with study participants. Additionally, their training will equip them to be available to provide technical troubleshooting assistance for participants.

### Measures

2.6

#### Demographic/health characteristics

2.6.1

At baseline (Time 1), a sociodemographic survey will collect information on sex, age, race, ethnicity, education, socioeconomic situation, relationship status, and time since death of the patient from cancer (in months). Information about comorbid conditions as a proxy of FCG health will be assessed using the standardized and validated 21-item Bayliss Comorbidity Index to identify number and types of chronic conditions and their level of interference in daily activities (57).

#### Acceptability/feasibility

2.6.2

At 12 weeks (Time 3) the self-reported 4-item Acceptability of Intervention Measure (AIM) (58) and the 4-item Feasibility of Intervention Measure (FIM) will be used (58). The AIM evaluates acceptability with questions about satisfaction and appeal of the intervention. The FIM evaluates feasibility with questions about benefits, ease of use, and manageability of the intervention. The number of FCGs consented vs. completed, and the number of times and weeks using the intervention will also be assessed.

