## Abstract

Friend and/or family caregivers (FCGs) of those with terminal cancer are heavily relied upon to address the emotional and physical needs of the patient facing death. Although increasing research has focused on testing supportive interventions for FCGs who deliver home-based care at end of life, limited attention has targeted strategies that support grief processing for bereaved FCGs during the months following the patients’ death. Both natural environments and meditation practices are shown to support directed attention, reflection, and the capacity to remain present with painful thoughts and emotions that are essential for grief processing. This mixed-method study assesses the potential of a new tailored online audio nature-meditative intervention to support grief recovery and healing among 70 bereaved cancer caregivers who are in the first year of bereavement. A primary goal is to assess the acceptability and feasibility of both content and delivery methods. Measures for the 6-week intervention include numbers eligible vs. consented; numbers consented vs. completed; number of weeks using the intervention, and self-report feasibility/acceptability. Potential effect size estimate data for future larger scale work will be collected at three time points: baseline (Time 1; study week 0), at the intervention end (Time 2; week 6), and at follow-up (Time 3; study week 12) on quality of life, bereavement (grief), directed attention, anxiety and depressive symptoms. Additionally, semi-structured interviews with a diverse representative subsample of 15 caregivers will be conducted at the end of the 12-week study to further assess acceptability and feasibility in more depth. Data analyses will include descriptive statistics, linear mixed models, and content analysis. Findings will be used to assess and enhance the intervention prior to wider scale testing with the long-term goal of establishing an evidence-based intervention for supporting bereaved cancer caregivers as they process grief and adapt to their loss.

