#### Power

2.7.1

Consistent with the analytic model (linear mixed-effect model, LMM) for estimating the change in the primary endpoint, QOL, a simulation-based approach (63) to estimate power to detect effect sizes (ESs) ranging from 0.2 (small) to 0.4 (moderate) is used. Because there is no existing literature on the within-participant correlation (
ρ
) of the outcome over time, three scenarios for 
ρ
(0.3, 0.4, 0.5) are used with 1,000 simulations for each of the three ESs (0.2, 0.3, 0.4) and the baseline sample sizes ranging from 40 to 70 for each simulation. For the power of 0.80 and *α* = 0.05, an initial sample size of 42 FCGs is adequate to detect an ES of 0.4 if 
ρ=
0.4 and 55 FCGs are needed if 
ρ=
0.3; 51 FCGs will be adequate to detect an ES of 0.3 if 
ρ=
0.5 and 65 FCGs are needed if 
ρ=
0.4; and more than 70 FCGs will be needed to detect an ES of 0.2 across all scenarios for 
ρ.
 To be conservative and within the budget, and assuming a 20% attrition rate by week 12, a total of 70 FCGs will be recruited.

Basic summary statistics for demographic characteristics and co-morbid conditions in FCG will be calculated. Because the study involves repeated measurements on the same FCG, basic summary statistics will be generated for each of the three time points. All analytic procedures envisioned for this exploratory project are consistent with general best practices, including recommendations made by the National Research Council panel on the prevention and treatment of missing data in clinical trials (64).

Any technology issues that emerge will be meticulously monitored and tracked. To estimate the change in FCGs’ outcomes across time, an LMM for continuous outcomes will be used. The results will be presented in both the original and standardized scales with estimated confidence intervals and no statistical hypothesis testing will be performed. The random effects will account for the correlation/covariance within the FCGs arising from the repeated measurements on each FCG. Further exploratory analyses will be conducted to assess the potential heterogeneity of the longitudinal profile of the outcomes by FCGs’ baseline characteristics (baseline QOL, age, gender, and relationship). Operationally, this heterogeneity will be assessed through interactions between time and any of the FCGs’ baseline characteristics. Estimates from these analyses will provide directional effects for a later larger-scale study.

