#### Interview data

2.7.2

The semi-structured interviews will provide rich contextual data on perceived acceptability and feasibility of the NBHM program to support bereavement. The sample will be carefully selected to ensure a broad range of perceptions in relation to socio-demographic background and user data (low to high engagement). The audio recordings will be transcribed verbatim. Transcriptions will be assessed for accuracy by verifying the text against the audio recordings. Similar to the team’s previous studies with hospice FCGs (65, 66), two trained investigators will first organize the results and identify major content categories independently, then compare and discuss until a consensus is achieved. Data summaries from each semi-structured interview will be assessed against the interview questions and then compared, with targeted attention to collective similarities, to inform content category development.

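### AIM, FIM and the interviews reach only caregivers still in the study at week 12, so self-reported acceptability probably runs high and the reasons of those who left are not heard

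*Protocol article*

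**What the plan says.** All references are to the protocol article.

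- **Timing of the scales (Acceptability/feasibility, 2.6.2).** "At 12 weeks (Time 3) the self-reported 4-item Acceptability of Intervention Measure (AIM"; the 4-item FIM is given at the same time. No other administration is stated. Grief, attention, quality of life and emotional symptoms are each measured at all three time points.
- **An earlier survey exists (Procedures, 2.3).** "At the end of the 6-week time, participants receive access to the Time 2 surveys".
- **Interview contact (Procedures, 2.3).** "Participants who consent to an interview will be contacted following completion of the week 12 surveys to schedule a date/time". The Abstract agrees on timing: a "subsample of 15 caregivers will be conducted at the end of the 12-week study".
- **Interview selection (Interview data, 2.7.2).** The sample is meant to cover a "broad range of perceptions in relation to socio-demographic background and user data (low to high engagement".
- **Attrition (Power, 2.7.1).** "assuming a 20% attrition rate by week 12, a total of 70 FCGs will be recruited".
- **Other measures of the same aim.** The analysis text under 2.7.1 assesses acceptability by consent among those approached and by completion among participants, and sets four modules in six weeks as the feasibility minimum. Fidelity (2.5) says the website logs module access and duration. The analysis text also forms latent classes from AIM and FIM and compares caregivers' characteristics and outcomes across them.

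**The concern.** Evaluating the acceptability and feasibility of content and delivery is the first research aim in the Introduction. The only instruments that ask caregivers what they thought of the modules are AIM, FIM and the interviews. All three are scheduled six weeks after the intervention ends. By then the weekly contacts of weeks 1 to 6 have stopped and the assumed attrition has occurred.

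If caregivers who disliked the modules leave more often than those who liked them, the ratings will look better than the experience of everyone enrolled. The latent classes inherit the same selection. The interviews, which are meant to guide refinement before a randomised trial, would miss the people with most to say about what did not work. Because AIM and FIM are taken once, a leaver has no earlier rating on the same scale to carry information forward. An opinion not asked for before someone leaves may not be recoverable.

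**Working it through.** **Inputs from the article.** Enrolled N = 70; attrition by week 12, m = 0.20 (Power).

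**Assumed inputs.** The proportion p_R of respondents who rate the intervention acceptable, and the proportion p_N of non-respondents who would have done so. The article gives neither, and defines no percentage-acceptable statistic for AIM. The proportion is used only for illustration; the same formula applies to a difference in mean scores.

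**Step 1. Expected respondents.** 70 × (1 − 0.20) = 56, so 14 are unobserved. The article does not state 56; it follows from its two figures. In reverse, 56 / 0.80 = 70.

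**Step 2. Bounds for all enrolled.** Lower: (1 − m) × p_R. Upper: (1 − m) × p_R + m. With p_R = 0.85 (assumed):
- lower: 0.80 × 0.85 = 0.68
- upper: 0.68 + 0.20 = 0.88

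**Step 3. Size and sign of the bias.** Bias = m × (p_R − p_N). With p_R = 0.85:

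| p_N (assumed) | Value for all 70 | Overstatement |
|---|---|---|
| 0 | 68% | 17 points |
| 0.30 | 0.68 + 0.20 × 0.30 = 74% | 11 points |
| 0.50 | 0.68 + 0.20 × 0.50 = 78% | 7 points |
| 0.85 | 85% | 0 |
| 1 | 88% | −3 points |

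**Step 4. Sensitivity to p_R.** With p_R = 0.80 the bounds are 64% and 84%, and the overstatement at p_N = 0.40 is 0.20 × 0.40 = 8 points. For comparison, the 95% half-width at n = 56 is 1.96 × √(0.80 × 0.20 / 56) = 10.5 points.

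**Step 5. What a week-6 administration would gain.** The width of the bounds equals m. The article gives no week-6 missingness, so take 5% to 15% as an assumption. With p_R = 0.80:
- m = 0.05: 76% to 81%
- m = 0.10: 72% to 82%
- m = 0.15: 68% to 83%

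At p_N = 0.40 the overstatement is 0.05 × 0.40 = 2 points to 0.15 × 0.40 = 6 points, against 8 points at m = 0.20.

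**Step 6. Interviews.** Procedures ties contact to completion of the week-12 surveys. Read plainly, a caregiver who does not complete them is not approached, so the 15 come from about 56 people.

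**The case against.** The strongest reply is that the first aim does not rest on these instruments alone. Consent rate, completion rate, the four-module minimum and the web logs need no week-12 response, and a caregiver who abandons the modules counts against the intervention in them. That stands. A reader might infer that the whole primary aim is answered only by those who stayed; the article does not support that. What remains is that a log shows that someone stopped, not why.

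Second, the direction of bias is not established. The article gives no reasons for dropout, and bereaved caregivers may leave for causes unrelated to the modules. If leavers think as stayers do, the bias is zero, and the upper bound of 88% exceeds the assumed 85%. This also stands: upward bias is the likely direction, not a fact.

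Third, a reader might see a contradiction between the interview timing and the wish for "user data (low to high engagement" coverage. There is none. Engagement there means logged use, and the 20% is loss from the study, not stopping the modules. Someone who opened one module can still answer at week 12 and be interviewed. But low use among those who stay is not the same as having left, so the gap is narrowed rather than closed. It is also fair that Procedures sets a contact time and does not state an exclusion; that leavers are not interviewed is the natural reading of it.

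Fourth, week 12 has a purpose. Participants keep access to the modules and use in weeks 7 to 12 is monitored, so a rating then covers sustained use. That argues for keeping week 12, not for omitting week 6.

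Finally, an exit form or a sensitivity analysis may sit in a full protocol or analysis plan. Their absence from the article is not counted here; the point rests on the timing and contact rules that the article does state.

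**Conclusion.** The point holds in a limited form. Self-reported acceptability and feasibility, the latent classes derived from them and the interviews come only from caregivers reached at week 12, about 56 of 70 under the plan's attrition. They are likely to overstate acceptability and leave out the reasons of those who left.

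The number of respondents follows from the article. The size of any overstatement does not. At an assumed 85% among respondents it ranges from 17 points too high to 3 points too low, and is 7 to 11 points too high if 30% to 50% of leavers would have approved. A bias of that order is comparable to the sampling error at this sample size.

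The study is exploratory, plans no hypothesis tests and states no AIM or FIM threshold that the bias could tip. This is therefore an inexpensive improvement to a stated aim, not a flaw that invalidates the study.

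**What to change.** 1. Add AIM and FIM to the existing Time 2 (week 6) survey and keep the week-12 administration as a repeat.
2. Offer the same eight items to anyone who withdraws, at the time of withdrawal.
3. Report AIM and FIM results with the number enrolled as well as the number responding, and include a sensitivity analysis for non-response.
4. Amend Procedures so that interviewees are selected from all enrollees who consent to an interview, including some who withdrew, and contact no longer depends on completing the week-12 surveys.

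The cost is eight items on a survey already being sent, the same items offered at withdrawal, and a changed selection rule for the 15 interviews. The Time 2 survey becomes slightly longer, and some leavers will not reply, so the selection is reduced rather than removed. The change works best before participants begin to leave.

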#### Grief

2.6.3

The PG-13-Revised Prolonged Grief (PG-13-R) scale, a validated 13-item self-report measure aimed to assess a protracted grief experience while also providing an indicator of the bereavement process, will be used (19) to assess grief symptoms at the three time points.

#### Directed attention

2.6.4

The Attention Function Index (AFI), a 16-item self-rating scale that measures perceived effectiveness in daily tasks that require cognitive function, an strong indicator of directed attention capacity. The AFI has demonstrated consistent reliability in both medical groups and among healthy adults (59) and will be used to assess directed attention at all three time points.

#### Quality of life

2.6.5

QOL domains, including physical, social and psychological functioning and health perceptions, will be measured using the PROMIS-29 (60, 61) at all three time points. The PROMIS is a collection of short-form profile instruments (social, psychological, and physical function, pain, fatigue, sleep disturbance, health satisfaction) (62).

#### Emotional symptoms

2.6.6

Depressive and anxiety symptoms will be assessed with the two respective PROMIS-29 short-forms (62) at all three time points.

### Data analysis

2.7

#### Power

2.7.1

Consistent with the analytic model (linear mixed-effect model, LMM) for estimating the change in the primary endpoint, QOL, a simulation-based approach (63) to estimate power to detect effect sizes (ESs) ranging from 0.2 (small) to 0.4 (moderate) is used. Because there is no existing literature on the within-participant correlation (
ρ
) of the outcome over time, three scenarios for 
ρ
(0.3, 0.4, 0.5) are used with 1,000 simulations for each of the three ESs (0.2, 0.3, 0.4) and the baseline sample sizes ranging from 40 to 70 for each simulation. For the power of 0.80 and *α* = 0.05, an initial sample size of 42 FCGs is adequate to detect an ES of 0.4 if 
ρ=
0.4 and 55 FCGs are needed if 
ρ=
0.3; 51 FCGs will be adequate to detect an ES of 0.3 if 
ρ=
0.5 and 65 FCGs are needed if 
ρ=
0.4; and more than 70 FCGs will be needed to detect an ES of 0.2 across all scenarios for 
ρ.
 To be conservative and within the budget, and assuming a 20% attrition rate by week 12, a total of 70 FCGs will be recruited.

Basic summary statistics for demographic characteristics and co-morbid conditions in FCG will be calculated. Because the study involves repeated measurements on the same FCG, basic summary statistics will be generated for each of the three time points. All analytic procedures envisioned for this exploratory project are consistent with general best practices, including recommendations made by the National Research Council panel on the prevention and treatment of missing data in clinical trials (64).

Any technology issues that emerge will be meticulously monitored and tracked. To estimate the change in FCGs’ outcomes across time, an LMM for continuous outcomes will be used. The results will be presented in both the original and standardized scales with estimated confidence intervals and no statistical hypothesis testing will be performed. The random effects will account for the correlation/covariance within the FCGs arising from the repeated measurements on each FCG. Further exploratory analyses will be conducted to assess the potential heterogeneity of the longitudinal profile of the outcomes by FCGs’ baseline characteristics (baseline QOL, age, gender, and relationship). Operationally, this heterogeneity will be assessed through interactions between time and any of the FCGs’ baseline characteristics. Estimates from these analyses will provide directional effects for a later larger-scale study.

Acceptability will be assessed at two levels: (1) among FCGs approached, how many consent to participate; and (2) among participants, how many complete the intervention. For feasibility we establish the following minimum parameters: FCGs must complete a minimum 4 modules during the 6-week period. The study will use latent class analysis to group FCGs into several clusters based on AIM and FIM measures and examine whether FCGs’ demographic and outcome measures differ by cluster. This analysis will inform the relationship between acceptability and feasibility and the outcomes. The web-tracking data will be used to examine the time of day and duration each FCG uses each module. An exploratory analysis of the association between timing and duration of use and endpoints will be performed to estimate a response curve and identify the minimum intervention use associated with meaningful improvement and the potential intervention saturation point (i.e., the effect plateaued).

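### The four sample sizes given for 80% power cannot all be right, and they justify a test that the plan says it will not run

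*Protocol article*

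**What the plan says.** All of this is in section 2.7.1 (Power) of the protocol article. The sizing is by simulation: "Consistent with the analytic model (linear mixed-effect model, LMM) for estimating the change in the primary endpoint, QOL, a simulation-based approach" is used, with "effect sizes (ESs) ranging from 0.2 (small) to 0.4 (moderate) is used", three values of rho and 1,000 simulations per scenario. The results are given "For the power of 0.80 and *α* = 0.05":

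- "an initial sample size of 42 FCGs is adequate to detect an ES of 0.4 if" rho is 0.4, and 55 are needed if rho is 0.3.
- "51 FCGs will be adequate to detect an ES of 0.3 if" rho is 0.5, and 65 are needed if rho is 0.4.
- More than 70 are needed for ES 0.2 at every rho.

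The section then settles the size: "assuming a 20% attrition rate by week 12, a total of 70 FCGs will be recruited". Two paragraphs later it says that results will be shown with "estimated confidence intervals and no statistical hypothesis testing will be performed". Section 2.1 (Study design) gives feasibility as the primary aim.

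The section does not state the time contrast, whether alpha is one- or two-sided, what SD standardises the ES, or whether the 20% attrition is already inside the simulated sample sizes.

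**The concern.** Two of the four figures share the same rho and differ only in ES, so they can be checked against each other without knowing the simulation settings. They fail that check. The other figures do not fit a common model either.

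Section 2.1 and the Limitations section say that the study will supply effect sizes, and section 2.7.1 says its estimates will serve a later, larger study. Someone planning that study will read these sample sizes as a statement of how sensitive this one is. If they are wrong, the reader is misled about how much an interval around a change of 0.3 SD can tell. The rationale is also of the wrong kind: alpha and power describe a test, whereas the planned output is an estimate with an interval, and its expected width is not given.

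**Working it through.** **Inputs (section 2.7.1).** Alpha 0.05; power 0.80; stated n of 42 (ES 0.4, rho 0.4), 55 (0.4, 0.3), 51 (0.3, 0.5) and 65 (0.3, 0.4); 1,000 simulations per scenario; 70 recruited; 20% attrition, so 70 × 0.8 = 56 at week 12.

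**Step 1. Attempt to reproduce the stated figures.** For a one-group change, n = V(z_alpha + z_power)²/ES², solved here with the noncentral t. V is the variance of the contrast in outcome-SD units. Under equal correlation, V = 2(1 − rho) for baseline to week 12, and V = 1.5(1 − rho) for baseline against the mean of both follow-ups.

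| Reading | 0.4, 0.4 | 0.4, 0.3 | 0.3, 0.5 | 0.3, 0.4 |
|---|---|---|---|---|
| Stated | 42 | 55 | 51 | 65 |
| Baseline to week 12, two-sided | 61 | 71 | 90 | 107 |
| Baseline to week 12, one-sided | 48 | 56 | 71 | 84 |
| Pooled follow-up, two-sided | 47 | 54 | 68 | 81 |
| Pooled follow-up, one-sided | 37 | 42 | 53 | 64 |

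Columns are ES, rho. Also tried: ES per visit step, ES in change-score SDs, a baseline-adjusted variance, an AR(1) correlation, the 2-df time test, and mixed-model versions with dropout. None gives all four.

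**Step 2. The check that needs none of the unstated settings.** At fixed rho, V, the critical value and any proportional attrition cancel, so n(0.3)/n(0.4) = (0.4/0.3)² = 1.78.

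- Stated ratio: 65/42 = 1.55.
- From 42: 42 × 1.78 = 74.7, about 75 (73 to 75 with a t correction).
- From 65: 65/1.78 = 36.6, about 37.
- If 42 is right, two-sided power at n = 65 for ES 0.3 is Φ(2.80 × √(65/42) × 0.75 − 1.96) = 74%.

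**Step 3. Simulation noise.** The Monte Carlo standard error at 80% power is √(0.8 × 0.2/1,000) = 1.3 points, so 74% is more than 4 standard errors low. As a direct check, V was left free and each n from 40 to 70 was given 1,000 runs (steps of 1 and independent runs assumed); the first n to reach 80% was taken. Getting 42 or more at ES 0.4 together with 65 or fewer at ES 0.3 occurred in under 0.5% of runs at the most favourable V, one- or two-sided.

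**Step 4. The rho ratios, which do need a model.** Under compound symmetry with ES in outcome SDs, n scales with (1 − rho).

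- 0.4 to 0.3 at ES 0.4: expected 0.7/0.6 = 1.17; stated 55/42 = 1.31.
- n × ES²/(1 − rho) should be constant; it is 11.2, 12.6, 9.2 and 9.8.

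**Step 5. What 70 can detect, by reading.** Two-sided, ES as total change in outcome SDs, all 70 retained:

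- ES 0.3, rho 0.4: 62% for baseline to week 12; 74% for pooled follow-up.
- ES 0.4, rho 0.3 and 0.4: 80% and 85% for baseline to week 12; 90% and 94% for pooled follow-up.

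With 20% attrition in a mixed model, ES 0.4 has 75% to 87% (baseline to week 12) or 87% to 96% (pooled) over rho 0.3 to 0.5. A one-sided pooled reading with the same attrition gives about 80% for ES 0.3 at rho 0.4.

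**Step 6. Precision with 56 at week 12.** Half-width = t(0.975, 55) × √(2(1 − rho)/56), with t = 2.004: 0.27 SD at rho 0.5, 0.29 at 0.4, 0.32 at 0.3.

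**The case against.** The strongest reply is that the simulation settings are unknown, so an outside recalculation cannot show that the design is underpowered. That is correct as far as it goes. A reader might infer from the two-sided baseline-to-week-12 row that the stated sizes have only about 56% to 69% power, that 70 recruits fail to deliver the sensitivity claimed, and that 0.4 SD is the true detectable change. The document does not support this, because it fixes neither that contrast, nor two-sided testing, nor that ES scale. Under a one-sided pooled-follow-up reading the required numbers are 37, 42, 53 and 64, and the stated sizes are close to adequate or better (79% to 89% power). If ES meant change per visit step, every stated size would be ample.

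Attrition is equally open. The section calls its figures initial and baseline sample sizes, which suggests that dropout may already be simulated; then 70 exceeds 65. If it is not, 56 is below 65, and 65/0.8 = 82 would be needed. A mixed model would also use week-6 data from people lost by week 12.

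The rho ratios depend on compound symmetry, which the section does not specify. The study is exploratory, feasibility comes first, and no decision hangs on 80% power. The section also says openly that 70 reflects the budget and that ES 0.2 is out of reach.

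All of this limits the consequence. None of it repairs 42 against 65 at the same rho: the one-sided pooled reading that fits 51 and 65 predicts 37 and 42 where 42 and 55 are stated. A condensed article may leave settings to a fuller document, but these figures are printed in the article itself.

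**Conclusion.** Wrong as written; moderate severity. The 42-versus-65 inconsistency (ratio 1.55 against 1.78) holds whatever the contrast, sidedness, ES standardiser or proportional attrition, provided these are the same in both scenarios. Simulation noise is not a credible explanation. The mismatch of the rho ratios is supporting evidence only, since it assumes compound symmetry.

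A shortfall at n = 70 is conditional. It applies to ES 0.3 at rho 0.4 under two-sided readings with ES as total change in outcome SDs. For ES 0.4, power is near or above 80% under most readings.

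Separately, the power rationale does not match an analysis that reports intervals and excludes testing. Neither defect calls for a different sample size.

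**What to change.** Keep n = 70. Then:

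- Either delete the four sample-size figures, or rerun the simulation and restate them with the contrast, sidedness, ES standardiser and attrition pattern given, including whether the sizes are before or after dropout.
- Justify 70 by the precision of the planned estimates. For example, with 56 participants at week 12 and equal correlation, the 95% confidence interval for baseline-to-week-12 change has a half-width of about 0.27 to 0.32 SD for rho from 0.5 to 0.3.
- Do not put 0.4 SD in as the detectable change unless the rerun supports it.

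The cost is wording and one rerun, with no extra participants. The restated figures may be less favourable than the present ones.
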